### Secondary outcomes

Incidence rates of secondary outcomes will be modeled as described for the primary outcome, through adjusted multivariable survival models.

### Analyses restricted to HIV+ cohort

#### Effect of antiretroviral therapy

To estimate the effect of antiretroviral medication on CVD risk, supplementary analysis will be performed in the cohort of HIV-infected individuals. Incidence rates of the primary outcome will be modeled using survival models similar to those described for the primary outcome, but with drug exposure as the main exposure variable. Drug exposure will be captured as time-dependent variables capturing cumulative exposure, updated for each month of exposure. Models of CVD risk according to exposure to individual drugs will be fitted for abacavir, tenofovir, efavirenz, atazanavir, lopinavir, darunavir, raltegravir, dolutegravir and elvitegravir. These drugs will be analyzed individually due to past signals of cardiovascular toxicity, prevalence of use in our cohort or insufficient data on cardiovascular toxicity available in the literature [21, 36–41]. Exposure to other antiretrovirals will be examined by drug class, as opposed to individually, because we would have insufficient power to detect effect of individual drugs.

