### Covariates and data collection

At the baseline visit, data will be collected (and entered into the electronical case report form) on socio-demographic factors, all past and current medication, all past and current medical conditions (including high blood pressure, diabetes, dyslipidemia, family history of premature CVD), presence of risk factors for HIV transmission, and lifestyle habits (smoking, alcohol consumption, illicit drug use and level of physical activity). For participants with HIV, date of diagnosis and presumed mode of transmission will also be recorded. A complete physical examination will be performed by the treating physician, and the study nurse will record vital signs, height, weight, and waist circumference.

At the subsequent yearly visits, data on medical history, medication history and lifestyle habits will be updated. Anthropometric measures and physical examination will be repeated. Data on primary and secondary outcomes will be recorded using specific case report forms. Additional file 4 presents the full contents of the case report form that will be filled out at each study visit.

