### Primary outcome

Longitudinal analyses of the CVD incidence/prospective analysis: This analysis will use prospective data and will focus on time until occurrence of the first incident CVD event, as defined by the composite outcome described above. It will be limited to subjects without a history of CVD at cohort entry. Analyses will employ time-to-event statistical methods including Cox proportional hazards (PH) model [33] and its flexible extensions. Time 0 will be defined as the cohort entry and subjects who do not develop CVD during the follow-up will be right-censored at the earliest of times of: loss to follow-up, administrative end of the study or a non-CVD death**.** In all models, the binary indicator of HIV infection will be the main ‘exposure’ and its effect on the risk (hazard) of incident CVD will be adjusted for “standard confounders”: age, sex, ethnicity, education, income, and illicit drug use. However, two different types of models will handle differently the CVD risk factors, to provide a better understanding of the mechanisms through which HIV infection may affect future CVD risks. The first model will adjust the effect of HIV for only the baseline values of CVD risk factors, in addition to “standard confounders”. This will allow us to estimate and test the potential differences in CVD incidence between HIV+ vs. HIV- individuals who had the same initial values of common CVD risk factors, at cohort entry. In contrast, the second model will adjust for the up-dated values of CVD risk factors, modeled by time-varying covariates, representing the most recent value observed until a given date during the follow-up. This model will permit testing if there is a ‘residual’ impact of HIV infection that is *not* mediated through longitudinal changes in common CVD risk factors. The independent association between HIV and CVD incidence will be then estimated through the adjusted HR, with 95% confidence intervals (CI). In both analyses the proportional hazards assumption we will be tested using a flexible extension of the Cox model [34, 35].

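### Each antiretroviral enters the CVD models only as cumulative exposure, so a risk tied to current or recent use could be diluted or missed

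*Protocol article*

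**What the plan says.** The section on the effect of antiretroviral therapy, under the analyses restricted to the HIV+ cohort, sets the aim: "To estimate the effect of antiretroviral medication on CVD risk, supplementary analysis will be performed in the cohort of HIV-infected individuals". The models resemble those for the primary outcome, "but with drug exposure as the main exposure variable". The exposure itself is defined once: "Drug exposure will be captured as time-dependent variables capturing cumulative exposure, updated for each month of exposure". That definition covers nine drugs modelled singly ("Models of CVD risk according to exposure to individual drugs will be fitted for abacavir, tenofovir, efavirenz, atazanavir, lopinavir, darunavir, raltegravir, dolutegravir and elvitegravir") and the remaining agents by class. The nine were chosen for differing reasons: "These drugs will be analyzed individually due to past signals of cardiovascular toxicity, prevalence of use in our cohort or insufficient data on cardiovascular toxicity".

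No term for current use, recent use, lagged use or recency-weighted use is given for any drug or class. The primary-outcome analysis section says "Analyses will employ time-to-event statistical methods including Cox proportional hazards (PH) model [33] and its flexible extensions", but the only task it gives to a flexible extension is testing proportional hazards. Under Covariates and data collection, the baseline visit records "socio-demographic factors, all past and current medication, all past and current medical conditions", and medication history is updated at later visits.

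**The concern.** A cumulative term makes the hazard a function of total months taken. Two participants with 60 months each get the same drug-related hazard, even if one stopped years before entry and the other is still on the drug. A participant in month 3 of a drug carries 3/60 = 5% of their log-hazard contribution when the term is linear.

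That suits a harm that builds up and persists. It does not suit a harm that is present while the drug is taken and recedes afterwards. Stopped exposure is likely to be common here: HIV+ participants must be at least 40 years old or at least 15 years infected, and the sensitivity-analysis section notes that they enter after differing durations of infection.

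At stake is the reading of a null result. A hazard ratio very close to 1 per month could be taken as reassurance about a named drug, although the model could not distinguish no effect from an on-treatment effect spread over past users.

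**Working it through.** **1. The plan's own figure.** The article gives no power for the drug analysis, so the main comparison serves as the anchor. Inputs from Power calculation: 3600 PY (HIV-), 3400 PY (HIV+), control rate 8 to 12 per 1000 PY, HR 1.90 to 1.72, alpha 0.05 (taken as two-sided; the article does not say).

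- Rate 8, HR 1.90: 3600 × 0.008 = 28.8 and 3400 × 0.008 × 1.90 = 51.7, total 80.5 events.
- Rate 12, HR 1.72: 3600 × 0.012 = 43.2 and 3400 × 0.012 × 1.72 = 70.2, total 113.4 events.
- Freedman-type power, Φ[√E × (HR-1)/(HR+1) - 1.96]: √80.5 × 0.90/2.90 - 1.96 = 0.82, giving 79.5%; √113.4 × 0.72/2.72 - 1.96 = 0.86, giving 80.5%.

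The stated 80% is reproduced. The HIV+ group alone should yield about 52 to 70 events, and the drug models have only these to work with.

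**2. Simulation on that scale.** 850 CVD-free HIV+ participants, 48 months, about 57 events, 400 runs per scenario. The following are assumptions, since the article gives none of them: 40% ever-users of the drug, 0 to 10 years of prior use, 30% to 70% of ever-users stopped before entry, 15% per year stopping on study. Cumulative exposure includes months before entry. The Monte Carlo standard error is at most √(0.25/400) = 2.5 points.

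| Truth | Planned cumulative term | Current-use-only model | Joint model |
|---|---|---|---|
| Current-use HR 1.9 | 15-32% | 41-62% | current-use term 32-40% |
| Cumulative HR 1.5 per 5 years | 61-66% | see below | cumulative term 48-54% |

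A separate set of runs on the same assumptions, with about 58 events, gives paired results (30% stopped / 70% stopped):

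- Current-use HR 1.9: planned 28% / 12%, current-use-only 58% / 48%, joint current-use term 37% / 37%.
- Current-use HR 2.5: planned 60% / 28%, current-use-only 91% / 74%, joint current-use term 68% / 58%.
- Cumulative HR 1.5 per 5 years: planned 69% / 64%, current-use-only 30% / 18%, joint cumulative term 52% / 54%. The joint model costs 69 - 52 = 17 and 64 - 54 = 10 points.

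**3. Sensitivity to the user mix.** True current-use HR 1.90, mean prior use 60 months, 0.8% stopping and 0.3% starting per month (all assumed), current-use-only model against planned term:

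- 30% past, 30% current users: 58-72% against 17-20%. The cumulative estimate is about 1.003 per month, or 1.17 to 1.19 per 5 years.
- 10% past, 40% current: 61-74% against about 32%.
- 45% past, 15% current: 52-56% against 10-12%.
- No past users at entry: 72% against 41%.

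Dilution grows with the share of past users. Some loss remains without any, because a linear month count fits an on/off effect poorly.

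**The case against.** Cumulative exposure is a recognised metric and is consistent with the article's own reasoning. The study hypothesis is about chronic inflammation and accelerated aging, and the viral-load analysis uses a cumulative area under the curve. Where harm truly accumulates, the planned term is the best of the three and a current-use-only model does poorly (30% / 18% against 69% / 64%). This stands. A reader might infer that the planned metric is wrong; the documents do not support that, because they establish neither risk shape and the cited drug studies are not at hand.

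A reader might also infer that a current-use term added beside the cumulative one recovers the power of the current-use-only model at little cost. It does not. At HR 1.9 the joint term reaches 32-40% rather than 41-62%, and the cumulative term loses clear precision.

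The text is also looser than a strict reading suggests. It does not say that months before entry count, though collecting past medication points that way. If only months on study counted, past users would sit near zero and the dilution would differ. Linearity is not stated either.

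Finally, recency windows and lags are commonly left to an analysis plan, and their absence alone would be no finding. But the article does fix the metric, its monthly updating and the drug list, so relying on cumulative exposure alone is a stated choice.

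**Conclusion.** The point holds as a limitation of a single exposure metric. If a drug's CVD risk follows current or recent use, the planned term has roughly 15-32% power at HR 1.9 and would report an effect of about 1.03 to 1.04 per year. It also cannot tell an on-treatment pattern from an accumulating one. These figures rest on the assumed user mix, prior duration and stopping rates, on pre-entry months being counted, on a linear term, and on about 57 events.

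The harm is conditional on the risk shape. The analysis is supplementary, power per drug is limited under any coding, and the primary HIV+ versus HIV- comparison is unaffected.

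**What to change.** In the section on the effect of antiretroviral therapy:

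- Keep the cumulative-exposure model as planned, and state whether months before cohort entry count.
- For each of the nine named drugs, prespecify a second model with time-dependent current/recent use (use now or within the last 6 months, versus none).
- Prespecify a joint model with both terms as a secondary analysis to separate the two patterns.
- Report all of them as supplementary, and do not read a null cumulative estimate alone as absence of risk.

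No new data are needed, because past and current medication is recorded at baseline and updated, and exposure is already built by month. The cost is one or two more models per drug (9 to 18 in all), more comparisons in a supplementary analysis, and a clearly less precise cumulative term, in the joint model only.

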### Nadir CD4 and HIV viral load

Lymphocyte CD4 nadir is an important variable in HIV, as it reflects the depth of the immune system suppression by the virus. It can also be used as an indirect proxy for unknown HIV infection date [36]. A survival model will be fitted with nadir CD4 (coded as a continuous variable) as the exposure variable and incidence of CVD as the outcome. Similarly, the cumulative effect of unsuppressed viral replication will be analysed, as it has been shown to be correlated with mortality in HIV infection [42]. Unsuppressed viral load leads to immune activation and inflammation, which, according to our research hypothesis, lead to CVD. In a survival model, the time-dependent, cumulative area under the curve of viral load measurements will be used as the exposure variable, with incidence of CVD as the outcome.

### Pre-planned sub-studies

#### Sub study 1 - characterization of atherosclerotic plaque

Lo reported increased prevalence of subclinical coronary atherosclerotic disease in HIV [43]. It is yet unclear if the composition of the atherosclerotic plaque in HIV is similar to that seen in the general population [36, 43–45]. More data are needed to characterize the atherosclerotic process, with possible implications for screening and treatment. In this sub-sub-study, 5 cardiac imaging modalities will be applied to characterize the atherosclerosis in HIV positive patients and compare it to that in HIV-negative controls: 1) positron emitting tomography (PET) scan of the ascending aorta and carotid arteries 2)carotid arteries ultrasound with measurement of intima-media thickness 3) cardiac computed tomography scan without injection of contrast media, 4) cardiac computed tomography scan with injection of contrast media, and 5) intravascular coronary ultrasound (in patients for whom coronary angiogram is clinically indicated). Most imaging modalities will be cross-sectional, but cardiac computed tomography scan and carotid arteries ultrasound will be repeated to assess progression of coronary artery disease.

### Hypothesis

Atherosclerotic plaque has a different composition in HIV infected individuals, which can be described by imaging modalities.

### Outcomes

For each of the imaging modalities, the primary outcome is difference in atherosclerotic plaque presence and composition between HIV+ and HIV-. For repeated measures (cardiac scan with contrast media), the outcomes include rate of progression of total plaque volume.

### Population and setting

Participants recruited in the Montreal study sites will be eligible to this sub-study. Participants with a moderate Framingham risk score (ranging from 5 to 20%) will be asked to take part in this sub-study. Computed tomography scans, carotid ultrasound and vascular PET scans will be done at the Centre Hospitalier de l’Université de Montréal radiology core lab. Coronary angiograms and intravascular ultrasound will be done at the CHUM coronary catheter laboratory. Projected sample sizes have been calculated individually for each imaging modalities to ensure sufficient power to detect clinically meaningful differences. We expect to perform 30 cardiac PET scans, 200 intima-media measurements, 200 non-contrast media cardiac scans, 190 contrast-media cardiac scans, and 100 intravascular ultrasounds.

#### Sub-study 2-characterization of dysglycemia

There are conflicting results in the literature regarding relative prevalence and determinants of dysglycemia (defined as impaired fasting glucose, impaired glucose tolerance or diabetes) in HIV-infected patients compared to the HIV-negative population [46–49]. Antiretrovirals, lipodystrophy, and altered metabolism due to long-lasting inflammation could contribute to development of dysglycemia in this population [49, 50]. In this sub-study, oral glucose tolerance tests will be used to assess patients at risk of or with known dysglycemia in a prospective fashion, with levels of biomarkers to further characterize the nature of HIV-associated dysglycemia.

### Hypothesis

Dysglycemia in HIV infection is associated with a different metabolic profile. Precisely, we hypothesize there will be more endothelial dysfunction (as measured by increased ICAM1, VCAM1, and E-selectin), more coagulation activation (as measured by increased PAI-1 and fibrinogen), more oxidative stress (as measured by oxidized-LDL), and more inflammation (as measured by IL-6, TNF-α, CRP) in HIV+ than in HIV- patients with dysglycemia.

### Outcomes

The primary outcome is difference in area under the curve for the biomarkers throughout the oral glucose tolerance test between HIV+ and HIV- patients.

### Population and settings

All patients from the main cohort recruited in the Montréal sites with fasting plasma glucose > = to 5.6 mmol/l or HbA1c > = 5.6% will be asked to undergo an oral glucose tolerance test to screen for dysglycemia. Serum will be banked during the oral glucose tolerance tests, and patients with abnormalities in glucose metabolism will have their sample analyzed for the biomarkers of interest (see hypothesis). Measurements will be done in the metabolism core lab of the CHUM. According to the incidence of dysglycemia, we aim to perform about 150 oral glucose tolerance tests, and to fully analyse serum for biomarkers in 1/3 (50). This will grant 90% power at alpha 0.05 to detect a 10% difference in oxidized LDL between the HIV + and HIV- patients, with similar power for the other biomarkers.

#### Sub-study 3-characterization of immune profile in CVD

Globally impaired immunity secondary to HIV infection might contribute to the risk of CVD in HIV infected individuals via several pathways. Of particular interest is the depletion of Th17 lymphocytes, leading to microbial translocation from the gut, sustained immune activation, and eventually immune senescence [51–55]. In this sub-study, we will perform cross sectional immunological studies to better characterize the contribution of various immune profiles on development of CVD, and how those differ between HIV+ and HIV- individuals.

### Hypothesis

CVD associated with HIV is immunologically distinct from CVD in HIV uninfected patients: impaired immunity induced by HIV infection leads to an immune risk profile that contributes to development of premature CVD.

### Outcomes

Immunological analyses will focus on Th17 paucity, monocyte activation, Cytomegalovirus infection, and presence of an immune risk phenotype characterised by T-cell senescence and immune activation. The primary outcomes are specific to each of those three aspects. They involve measures of correlations between immune profiles and total coronary plaque volume, in participants with and without HIV.

### Population and setting

For this sub study, the presence of CVD will be measured as total coronary plaque volume, which is measured on injected cardiac Computed tomography (CT) scan. Banked samples from all patients who undergo injected cardiac CT scan will be analyzed. The planned sample size is 190 patients in total.

#### Sub-study 4 - characterization of genetic profile in CVD

Several studies have reported that a genetic risk score is associated with incident and prevalent CVD [56–58]. It remains unknown whether a genetic predisposition for atherosclerosis could also potentiate HIV-specific mechanisms for CVD. We propose to evaluate whether a genetic risk score comprised of 30 single nucleotide polymorphisms (already validated in genome-wide association studies) can predict the presence of CVD, and whether the risk score is more strongly associated with CVD in HIV+ as compared to HIV- individuals.

### Hypothesis

A genetic risk score will be more strongly associated with subclinical CVD in HIV+ than in HIV- participants.

### Outcomes

The primary outcome is the difference in risk scores between HIV+ and HIV- patients with CVD.

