### Statistical considerations

#### Power calculation

Based on data from both our local HIV database and our pilot study [27, 28], we expect the HIV positive population to be 80% male, with a mean age of 50 years at the beginning of the study. Based on data from the Framingham study, expected rates of our primary outcome in HIV-negative participants are 10/1000 person-years for men and 4/1000 person-years for women in the 45–54 age group [29]. The rates more than double for the 55–64 age group [29]. Accordingly, we assume the overall CVD incidence rate in HIV-negative controls will range between 8/1000 PY and 12/1000 PY. Analysis for the primary outcome will be limited to subjects who are free of CVD at baseline. We expect that, at baseline, up 10% of HIV- and 15% of HIV+ subjects will have prevalent CVD [29]. Finally, we assume that an average CVD-free subject will contribute 4 years of follow-up (of the maximum potential follow-up of 5 years). Under these assumptions, the recruitment of 1000 subjects in each group (implying that 900 HIV- and 850 HIV+ subjects will be free of CVD at baseline, contributing 3600 and 3400 PY of follow-up) will yield 80% power with alpha = 0.05 to detect hazard ratios of 1.72 to 1.90 for the primary composite outcomeof CVD. These risk increases are clinically plausible and are actually lower than the more than 2-fold (HR > 2.0) increases in the risk of major CVD events associated with HIV infection [30]. Some studies have reported higher HRs for specific sub-populations or CVD events, e.g. HR 4.0 for risk of stroke among younger subjects [31]. All sample size calculations were done with the PASS software [32].

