### Population and settings

The genetic risk score will be measured in all patients from the prospective cohort.

For sub-studies 1–4, details of the planned statistical analysis are presented in Additional file 5

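### Sub-study 4's primary outcome compares genetic scores among CVD cases only, so it reflects the hypothesised HIV-by-score interaction only under conditions that the protocol neither states nor secures

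*Protocol article*

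**What the plan says.** All the relevant text is in the protocol article under Sub-study 4.

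- The introductory paragraph sets two aims for a 30-SNP score: whether it "can predict the presence of CVD, and whether the risk score is more strongly associated with CVD in HIV+ as compared to HIV- individuals".
- The Hypothesis section reads: "A genetic risk score will be more strongly associated with subclinical CVD in HIV+ than in HIV- participants".
- The Outcomes section reads: "The primary outcome is the difference in risk scores between HIV+ and HIV- patients with CVD".
- The Population and settings section reads: "The genetic risk score will be measured in all patients from the prospective cohort". For sub-studies 1 to 4 it adds that "details of the planned statistical analysis are presented in Additional file 5". That file is not shown.

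The article gives no sample size, power or effect size for this sub-study. The only CVD prevalences it gives are in the Power calculation section, for clinical CVD at baseline: "up 10% of HIV- and 15% of HIV+ subjects will have prevalent CVD".

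**The concern.** The aim and the hypothesis compare two associations: score with CVD in HIV+, against score with CVD in HIV-. The primary outcome compares two means, both taken in people who already have CVD. Participants without CVD do not enter it.

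Three things follow.

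- The first aim, prediction of CVD by the score, cannot be addressed by this outcome in either group.
- The second aim is addressed only by proxy. If HIV adds to CVD risk and CVD is common, HIV+ participants reach case status with less genetic liability on average. Their mean score among cases is then lower with no interaction present. Any difference in mean score between the HIV groups as a whole, for example through ancestry, also passes straight into the contrast.
- The Outcomes section says CVD where the Hypothesis says subclinical CVD, so the case definition is not fixed. The size of the problem depends on how common the cases are.

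At stake is the interpretation of the sub-study's main result. A given value of the contrast could arise whether the hypothesis is true or false.

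**Working it through.** The article states no figure for this sub-study, so there is none to reproduce. The check compares the stated outcome with the quantity in the hypothesis.

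**Inputs from the article.** Prevalent CVD of 10% (HIV-) and 15% (HIV+), and 1000 participants per group (Power calculation). Frequency matching is on age, sex and smoking only (Study participants). Ethnicity is listed among the adjustment variables of the main model (Statistical analysis, Primary outcome).

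**Assumptions.** Score normal with SD 1 in each HIV group; logistic risk of CVD in the score; odds ratio (OR) per SD of 1.5 in HIV-, and 1.5 (no interaction) or 2.0 (interaction) in HIV+. The article gives no subclinical prevalence, so 30%/45%, 40%/60% and 40%/75% (HIV-/HIV+) are assumed.

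**Formulas.** In group g with mean score m_g, P(CVD | s) = 1/(1 + exp(-(a_g + b_g s))), with b_g = ln OR_g and a_g solved to give the prevalence p_g. Then:

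- mean score in cases: C_g = E[s P(CVD | s)] / p_g
- mean score in non-cases: N_g = E[s (1 - P(CVD | s))] / (1 - p_g)
- stated outcome: C(HIV+) - C(HIV-)
- contrast matching the hypothesis: [C - N](HIV+) - [C - N](HIV-)

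**Rare-disease limit.** As p_g goes to 0, C_g tends to m_g + ln OR_g. The stated outcome then tends to (m+ - m-) + (ln OR+ - ln OR-). With equal means it is the interaction itself: 0 for 1.5 vs 1.5, and ln 2.0 - ln 1.5 = 0.693 - 0.405 = 0.288 for 2.0 vs 1.5. This shows both what the case-only contrast can do and which two conditions it needs.

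**Equal mean scores, by numerical integration.**

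| Prevalence HIV-/HIV+ | Case means HIV-/HIV+, OR 1.5 in both | Stated outcome, no interaction | HIV+ OR at which it is zero | Stated outcome, OR 2.0 vs 1.5 | Hypothesis contrast, OR 2.0 vs 1.5 |
|---|---|---|---|---|---|
| 10%/15% (article) | 0.359 / 0.337 | -0.02 SD | 1.54 | +0.19 SD | +0.25 SD |
| 30%/45% (assumed) | 0.275 / 0.215 | -0.06 SD | 1.70 | +0.07 SD | +0.23 SD |
| 40%/60% (assumed) | 0.234 / 0.156 | -0.08 SD | 1.89 | +0.02 SD | +0.24 SD |
| 40%/75% (assumed) | 0.234 / 0.098 | -0.14 SD | 3.14 | -0.07 SD | +0.25 SD |

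With equal odds ratios, the hypothesis contrast is 0.00 SD in every row. The stated outcome is about -0.08 SD at 40%/60% without interaction and about -0.07 SD at 40%/75% with it. Nearly the same value thus arises with the hypothesis false and with it true.

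**Unequal mean scores, at 10%/15% (shift sizes are assumptions).**

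- No interaction, HIV+ mean 0.2 SD higher: case means 0.537 and 0.359, stated outcome +0.18 SD, hypothesis contrast 0.00. With 1000 x 15% = 150 and 1000 x 10% = 100 cases, a two-sample test rejects about 28% of the time.
- Interaction (2.0 vs 1.5), HIV+ mean 0.25 SD lower: case means 0.304 and 0.359, stated outcome -0.06 SD, hypothesis contrast +0.25 SD.

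**The case against.** The strongest reply has four parts.

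1. *A case-only contrast is a recognised test of multiplicative interaction.* This stands. A reader might infer that the stated outcome does not test the hypothesis at all, and the article does not support that. At its own 10%/15%, with equal scores, the contrast is -0.02 SD without interaction and +0.19 SD with odds ratios of 2.0 vs 1.5. It behaves there nearly as an interaction test. What remains is that the necessary conditions are neither stated nor secured.

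2. *The larger biases rest on prevalences that the article does not give.* Also true: 30% to 75% is assumed. The Hypothesis nevertheless names subclinical CVD, and nothing in the article says that it is rare.

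3. *No ancestry imbalance is shown.* Correct, and the shifts above only illustrate the mechanism. But matching covers age, sex and smoking, so equal score distributions are not secured by design.

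4. *The analysis is in Additional file 5, which may contain an interaction model.* It may. Scoring the whole cohort is consistent with an analysis that uses non-cases. A reader might therefore also go too far in concluding that the sub-study will report the wrong answer, because the full analysis is not visible. The point here is not missing detail. The article positively states a primary outcome that does not match its own hypothesis, and an interaction model elsewhere would leave that statement to be corrected.

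**Conclusion.** The mismatch between outcome and hypothesis holds on the text. The stated outcome cannot give the score-CVD association in either HIV group, and it stands in for the interaction only if the score is independent of HIV status and CVD is rare.

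The consequence depends on the case definition. For clinical CVD at the article's prevalences with equal scores, the bias is minor (-0.02 SD; zero at an HIV+ odds ratio of 1.54 against 1.50). For subclinical CVD at an assumed 30%/45% or 40%/60%, it is -0.06 or -0.08 SD, and the hypothesised effect must reach an odds ratio of about 1.70 or 1.89 before the contrast stops being negative. A difference in mean score by ancestry would add a direct shift in either direction. These sizes assume a normal score, a logistic model and an odds ratio of 1.5 per SD in HIV-.

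Severity is moderate. The fault is in the primary outcome of one sub-study; the cohort's primary outcome and its power are untouched.

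**What to change.** Redefine the primary outcome of Sub-study 4 as the HIV-by-score interaction: the product term in a regression of CVD on HIV status, score and their product, adjusted for age, sex and ethnicity or genetic ancestry. Include all scored participants who have the CVD measure, with and without CVD. In addition:

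- state one CVD definition and use it in the aim, hypothesis and outcome;
- report the score-CVD association within each HIV group, which also answers the first aim;
- keep the score difference among cases as descriptive;
- check Additional file 5 and align it with this.

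The cost is mainly wording, since scoring is already planned for everyone. There are two small downsides. The interaction estimate is less precise than a case-only contrast when the case-only conditions do hold. And if CVD is defined by coronary plaque on contrast CT, the analysis is limited to those scanned, about 190 by the plans for Sub-studies 1 and 3.
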